### RQ3 analyses: Mediating effects

As described in more detail above, hypotheses regarding mediating effects are tested on the basis of the method proposed by Preacher & Hayes [101]. Below, we report power analysis statistics for the significance tests of the indirect effect ab from the mediation analyses. These statistics consist of bootstrapping statistics for the beta coefficients (means and confidence intervals), *p*-values (bootstrapped p-values, mean p-values and their confidence intervals), and power calculations. We also present adjusted p-value statistics as well as power calculations as based upon adjusted p-values. It should be stressed, that power calculations were done somewhat differentially than it was done for the coefficients in the mixed effects regression models. In these analyses, the indirect effect ab of a moderation analysis in a given bootstrap sample was deemed significant, firstly, if c, b and a were significant, and secondly, if ab - as estimated by the Sobel test - was significant. Power analyses were therefore conducted on the basis of the p-values of all of these parameters. Adjusted power is calculated on the basis of adjusted p-values of the Sobel test only, although it might be more accurate to also adjust the *p*-values of c, b and a in the power calculation.

Statistics of tests of the indirect effects are shown in Table 5. Apart for the EF mediation effects on the DIL and SEMLA interventions on TEC, these power analyses indicate strong power for all mediation effects under the assumed effect sizes shown Table 3. However, for the math mediation effect on the SEMLA intervention effect on EF (i.e., “EF-by-Math”), the Beta coefficient is negative. This is in line with the previous observation of negative Beta coefficient for the intervention effect of SEMLA on Math. This suggests that the SEMLA intervention effect has a negative impact on children’s early maths skills, which in turn leads to a negative math mediation effect of the SEMLA intervention on EF.

**Table 5 Tab5:** Simulation statistics of the analyses of the indirect effects in the mediation tests, testing mediation effects of EF on the intervention effects on TEC (TEC-by-EF), Language (Language-by-EF), Math (Math-by-EF), the mediation effect of Language on the intervention effect on EF (EF-by-Language), and the mediation effect of Math on the intervention effect of EF (EF-by-Math)

Statistics	TEC-by-EF		Language-by-EF		Math-by-EF		EF-by-Language		EF-by-Math	
	DIL	SEMLA	DIL	SEMLA	DIL	SEMLA	DIL	SEMLA	DIL	SEMLA
Mean Beta	0.54	0.20	0.51	0.31	0.08	0.05	0.37	0.68	0.36	−0.59
Beta.lower	0.24	0.04	0.24	0.06	0.03	0.01	0.20	0.48	0.22	−0.90
Beta.upper	0.88	0.41	0.76	0.55	0.12	0.09	0.55	0.89	0.51	−0.31
boot.p	.000	.008	.000	.008	.000	.008	.000	.000	.000	.000
mean.p	.004	.064	.003	.052	.003	.052	.004	.000	.001	.001
p.upper	.000	.000	.000	.000	.000	.000	.000	.000	.000	.000
p.lower	.025	.533	.020	.525	.022	.525	.032	.000	.007	.001
Power	0.51	0.75	0.97	0.81	0.99	0.81	0.97	0.82	0.99	0.82
adjusted.p mean	.006	.082	.005	.067	.005	.067	.006	.000	.002	.001
adjusted.p.upper	.000	.000	.000	.000	.000	.000	.000	.000	.000	.000
adjusted.p.lower	.048	.620	.042	.620	.042	.620	.056	.000	.014	.003
adjusted.power	0.51	0.67	0.96	0.77	0.97	0.77	0.96	0.82	0.99	0.81

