### RQ3 analyses: Mediating effects

Hypotheses regarding mediating effects are tested on the basis of the method proposed by Preacher & Hayes [101]. Preacher & Hayes [101] differentiate between the *total effect* of X on Y, which is the effect when not taking into account the mediator M, the *direct effect* of X on Y, the effect when the mediator is taken into account, and the *indirect effect* of X on Y, the effect of X on Y as mediated by M. In order to estimate the indirect effect, Preacher & Hayes [101] propose a method of fitting the following three regression models:

Y_i_ = α + cX_i_ + ε_i_ where *c* estimates the total effect

M_i_ = α + aX_i_ + ε_i_ where *a* estimates the effect of X on the mediator M

Y_i_ = α + c’X_i_ + bX_i_ + ε_i_ where *c’* estimates the direct effect of X on Y and *b* the effect of M on Y when controlling for X

A prerequisite for a mediation effect is that c is significant (that is, that there is an effect of X on Y at all, that a is significant (that is, that there is an effect of X on M), and that b is significant (that is, there is an effect of M on Y over and above that of X).

The indirect effect, that is, the mediation effect, is equal to the product of a and b, *ab*, which in most cases is equivalent to the difference between c and c’. Several ways of calculating the standard error of ab have been proposed (e.g., [102, 103]; and see [104], for a review). However, following Preacher & Hayes [101], the standard error and significance of ab is calculated on the basis of bootstrapping. Here, ab is calculated on the basis of 10,000 bootstrap samples, yielding a distribution of 10,000 ab estimates. The point estimate of ab is simply the mean of that bootstrapped distribution, the standard error is the standard deviation of the distribution, and the confidence interval is the 5 and 95% percentile of the distribution. The bootstrapped *p* value of ab is the proportion of ab estimates that is equal to or lower than zero and the total number of ab estimates.

In order for a null hypothesis of no mediation effect to be rejected, the effects of a, b, c and ab, as estimated on the basis of bootstrapping, need to be significant.

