### RQ1 and RQ2 analyses: Intervention effects and intervention differences

Since RQ2 hypotheses regarding intervention differences will be tested on the basis of planned comparisons testing differences between the intervention effects in the RQ1 hypothesis models, RQ1 and RQ2 analyses will be tested together. As mentioned above, we will apply p-value correction to the p-values of coefficients that address the hypotheses.

Table 4 shows the statistics for the intervention model coefficients, including the planned comparisons of the intervention differences, for all RQ1 and RQ2 models. These models test intervention effects and intervention differences on EF, Language, Math and TEC. Apart for the SEMLA intervention effect on EF score and the DIL intervention effect on TEC, these analyses’ power show strong power for all intervention effects and intervention differences under the assumed effect sizes (see Table 3). Notably, the Beta coefficient for the SEMLA intervention on math is negative, indicating that SEMLA in fact might have a negative effect on early maths skills.

**Table 4 Tab4:** Simulation statistics for the intervention model coefficients of all RQ1 and RQ2 models

Statistic	EFScore			Language Score			Math			TEC		
	DIL	SEMLA	DIL vs. SEMLA	DIL	SEMLA	DIL vs. SEMLA	DIL	SEMLA	DIL vs. SEMLA	DIL	SEMLA	DIL vs. SEMLA
Mean Beta	0.85	0.30	0.55	0.49	1.06	−0.57	0.10	−0.08	0.18	0.02	0.75	−0.73
Beta.lower	0.55	−0.03	0.22	0.21	0.78	−0.87	0.06	−0.14	0.11	−0.50	0.31	−1.18
Beta.upper	1.16	0.64	0.82	0.77	1.34	−0.28	0.13	−0.02	0.25	0.98	1.67	−0.31
boot.p	.000	.036	.000	.000	.000	.000	.000	.003	.000	.584	.002	.002
mean.p	.000	.096	.003	.008	.000	.003	.003	.029	.000	.424	.018	.022
p.lower	.000	.000	.000	.000	.000	.000	.000	.000	.000	.000	.000	.000
p.upper	.000	.774	.036	.080	.000	.033	.022	.326	.000	.971	.157	.195
Power	1.00	0.69	0.98	0.96	1.00	0.99	0.99	0.89	1.00	0.17	0.91	0.89
adj. p mean	.000	.118	.005	.010	.000	.001	.004	.038	.000	.472	.026	.031
adj. p.lower	.000	.000	.000	.000	.000	.000	.000	.000	.000	.000	.000	.000
adj. p.upper	.000	.816	.062	.130	.000	.050	.037	.408	.000	.975	.214	.252
adj. Power	1.00	0.61	0.97	0.94	1.00	0.97	0.98	0.86	1.00	0.16	0.87	0.85

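### Table 5 does not give the power of the planned RQ3 mediation test, and its implied power for SEMLA on EF and DIL on TEC disagrees with Table 4

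*Protocol article*

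**What the plan says.** **Planned test** (Statistical analysis, RQ3 analyses: Mediating effects). Three regressions are written with a child index only, without covariates or random intercepts. In them, c is the intervention effect on the outcome, a "estimates the effect of X on the mediator M", and b is the effect of the mediator given the intervention. For the product, "the standard error and significance of ab is calculated on the basis of bootstrapping", with 10,000 samples. The bootstrapped p "value of ab is the proportion of ab estimates that is equal to or lower than zero". To reject the null hypothesis of no mediation, "the effects of a, b, c and ab, as estimated on the basis of bootstrapping, need to be significant".

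**Power run** (the section of the same name under Power calculations). A mediation counted as significant "firstly, if c, b and a were significant, and secondly, if ab - as estimated by the Sobel test - was significant". For the adjusted figures, "Adjusted power is calculated on the basis of adjusted p-values of the Sobel test only". The article adds that adjusting c, b and a as well might be more accurate. After excepting the two TEC-by-EF effects, it concludes that "these power analyses indicate strong power for all mediation effects under the assumed effect sizes shown Table 3".

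**Direct intervention effects** (RQ1 and RQ2 analyses, Table 4). These come from the RQ1 mixed models, which have random intercepts for unit and preschool plus prescore, fidelity, ECERS and background variables. The text excludes two effects from strong power: "Apart for the SEMLA intervention effect on EF score and the DIL intervention effect on TEC".

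**The concern.** There are two separate difficulties.

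First, the rule whose power is reported is not the rule that will be applied. Both the test of ab and the reach of the false-discovery correction differ.

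Second, SEMLA on EF is path a or path c in every SEMLA column of Table 5. Table 4 gives that effect power 0.69 and the text declines to call it strong. Yet four mediations that require it to be significant are called strongly powered.

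The stake is interpretation. A null SEMLA mediation result would be read against about 80% power, when the article's cluster-respecting models support less for one of the required components.

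**Working it through.** The simulation cannot be rerun because the pilot data are not in the article. The check uses the printed tables and one inequality.

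**Step 1. Conditional ceiling.** If a, b, c and ab must all be significant, then

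power(mediation) ≤ min{power(a), power(c)}.

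Taking a and c from Table 4 (unadjusted power):

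| Mediation | c | a | Ceiling | Table 5 | Difference | Table 5 adjusted |
|---|---|---|---|---|---|---|
| TEC-by-EF, SEMLA | 0.91 | 0.69 | 0.69 | 0.75 | +0.06 | 0.67 |
| Language-by-EF, SEMLA | 1.00 | 0.69 | 0.69 | 0.81 | +0.12 | 0.77 |
| Math-by-EF, SEMLA | 0.89 | 0.69 | 0.69 | 0.81 | +0.12 | 0.77 |
| EF-by-Language, SEMLA | 0.69 | 1.00 | 0.69 | 0.82 | +0.13 | 0.82 |
| EF-by-Math, SEMLA | 0.69 | 0.89 | 0.69 | 0.82 | +0.13 | 0.81 |
| TEC-by-EF, DIL | 0.17 | 1.00 | 0.17 | 0.51 | +0.34 | 0.51 |
| Language-by-EF, DIL | 0.96 | 1.00 | 0.96 | 0.97 | +0.01 | 0.96 |
| Math-by-EF, DIL | 0.99 | 1.00 | 0.99 | 0.99 | 0.00 | 0.97 |
| EF-by-Language, DIL | 1.00 | 0.96 | 0.96 | 0.97 | +0.01 | 0.96 |
| EF-by-Math, DIL | 1.00 | 0.99 | 0.99 | 0.99 | 0.00 | 0.99 |

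The Monte Carlo standard error with 2000 samples is √(0.69 × 0.31 / 2000) ≈ 0.01. All five SEMLA figures and one DIL figure are clearly above the ceiling. The other four DIL figures are within 0.01 of it.

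The adjusted Table 5 figures left a and c unadjusted, so their matching ceiling is still 0.69. Four of the five adjusted SEMLA figures exceed it, and 0.67 does not.

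**Step 2. What Table 5 implies about its own components.** The Sobel statistic is z = 1/√(1/z_a² + 1/z_b²), which is smaller than both |z_a| and |z_b|. Where Sobel rejects, a and b therefore reject too (treating all as normal tests at the same level). Table 5 power is then the chance that Sobel and c both reject.

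- EF-by-Language, SEMLA: the 95% quantile of the Sobel p is .000 (the upper and lower row labels for p in Table 5 appear to be interchanged). At most 5% of runs fail on Sobel, so power for c, SEMLA on EF, lies between 0.82 and 0.82 + 0.05 = 0.87. Table 4 gives 0.69.
- TEC-by-EF, DIL: the 95% quantile is .025, so power for c, DIL on TEC, lies between 0.51 and 0.51 + 0.05 = 0.56. Table 4 gives 0.17.

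The same two effects, under the same Table 3 assumptions, thus have different power in the two tables.

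**Step 3. Direction of the Sobel substitution.** An illustrative single-level simulation assumed 108 children per arm (9 clusters × 12), unit residual SD, 400 replicates and 500 bootstrap draws. It compared a, b, c plus Sobel with a, b, c plus the bootstrap p as planned:

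| Assumed a, b, direct effect | With Sobel | With bootstrap |
|---|---|---|
| 0.34, 0.60, 0.15 | 0.52 | 0.52 |
| 0.40, 0.25, 0.30 | 0.55 | 0.66 |
| −0.45, 0.50, 0.60 | 0.62 | 0.00 |

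The third row matters for EF-by-Math under SEMLA, where Table 5 has mean ab −0.59 and a 5% to 95% range of −0.90 to −0.31. The implied SD is (0.90 − 0.31)/(2 × 1.645) = 0.179. An estimate above zero then has probability Φ(−0.59/0.179) = Φ(−3.29) ≈ 0.0005. A p-value that counts only estimates at or below zero would almost never fall under 0.05, so literal power is near 0 against the stated 0.82. The general Power calculations section switches the direction of the bootstrap p with the sign of the mean coefficient; the RQ3 definition does not.

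**The case against.** The strongest reply is that Table 4 is not a ceiling for Table 5. The inequality needs a and c from the same models, and the RQ3 section writes simple regressions while Table 4 comes from mixed models with covariates. The article says power was run on the models described, and that the mediation runs were done differently from the mixed-model ones. Table 5 is also coherent within itself: the four SEMLA figures outside TEC, 0.81 to 0.82, fit one shared SEMLA-on-EF path of about 0.82. This stands. A reader might infer an arithmetic error, or that no SEMLA mediation can reach 80%. The document supports neither. But the reply moves the difficulty rather than removing it: Table 5 then rests on models without the unit and preschool effects that the RQ1 section and the Discussion use to handle the clustering, and the article does not explain the discrepancy.

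A reader might also set the adjusted figures against 0.61, the adjusted Table 4 power for SEMLA on EF. That does not fit, because a and c were not adjusted in Table 5. The 0.61 ceiling applies only if they are.

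The Sobel test and the partial adjustment are disclosed, and both TEC-by-EF effects, including the 34-point gap, are already excluded from the strong-power claim. Both points are correct. Disclosure still does not turn the figures into the power of the planned test, and four SEMLA mediations remain under the claim. A reader might further infer that the Sobel swap by itself inflates power; step 3 shows no fixed direction.

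Finally, testing ended in June 2017, so restated power cannot change the sample. That limits the consequence to how results are read.

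**Conclusion.** The point holds in this form. Table 5 reports power for a, b, c plus Sobel with only the Sobel p adjusted, while the plan tests a, b, c plus a bootstrapped ab. Separately, Table 5 implies about 0.82 for SEMLA on EF and about 0.51 for DIL on TEC, against 0.69 and 0.17 in Table 4.

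The likely cause, which the article does not state, is single-level regressions in Table 5 against mixed models with covariates in Table 4. The tables do not show how much of the gap comes from clustering and how much from covariates.

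Conditional on a and c coming from the RQ1 models, power is at most 0.69 for every SEMLA mediation (6 to 13 points below the stated figures) and at most 0.17 for TEC-by-EF under DIL (34 points below). The exact power under the planned rule cannot be computed without the pilot data.

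**What to change.** 1. Change the RQ3 models for a, b and c to include unit and preschool random intercepts, as in RQ1.
2. State the direction of the bootstrap p for ab, so that a negative indirect effect is handled as intended.
3. Rerun the Table 5 simulation under the rule that will be used: bootstrapped ab, with the false-discovery correction applied to the p-value that decides, the largest of those for a, b, c and ab. Restate the power.
4. Until then, label Table 5 as power for a Sobel-based rule whose component powers differ from Table 4, and withdraw the strong-power statement for the SEMLA mediations.

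The cost is one simulation rerun, which can use fewer bootstrap draws per sample than the final analysis, and less favourable stated power. No new data are needed.

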### RQ4 analyses: Moderating effects

As described above, RQ4 hypotheses concern moderating effects, that is, interaction effects between interventions and other variables. In Table 6, we report power analysis statistics for the significance tests of the critical interaction effects. These concern interaction effects between SES and the intervention effects on EF, Language, Math and TEC, as well as the interaction effect between EF score at pretesting and the EF posttest score. Again, we report bootstrapping statistics for the beta coefficients (means and confidence intervals), *p*-values (bootstrapped p-values, mean p-values and their confidence intervals), power calculations, as well as adjusted p-value statistics and power calculations based upon adjusted p-values. As can been seen in the table, moderating effects of SES on EF and Language have very high power under the assumed effect sizes. These moderating effects also show the expected direction in that all of the beta coefficients are negative. In other words, the intervention effects on EF and Language can be expected to be stronger for low-SES children than for high-SES children. The moderating effects of SES on TEC, on the other hand, show a different pattern. First, power for the SES moderation effect on the SEMLA intervention effect on TEC is low, indicating that no effect can be expected. Second, the beta coefficient of the SES moderation on the DIL intervention effect is positive, contrary to the hypothesis. In other words, this indicates that it is high-SES children, rather than low-SES children that will show a stronger intervention effect of SEMLA on TEC.

**Table 6 Tab6:** Simulation statistics of analyses of moderating effects, in terms of interactions between SES and the intervention effects on EF, Language, and TEC, and the interaction between EF pretest score and the intervention effects on EF

Statistic	EFScore		LanguageScore		TEC		EFScore	
	DIL × SES	SEMLA × SES	DIL × SES	SEMLA × SES	DIL × SES	SEMLA × SES	DIL × EFpre	SEMLA × EFpre
Mean Beta	−0.54	−0.53	−0.79	−0.89	0.65	0.24	−0.23	0.30
Beta.lower	−0.74	−0.71	−0.96	−1.08	0.28	−0.09	−0.41	0.13
Beta.upper	−0.33	− 0.36	−0.61	− 0.70	1.05	0.59	−0.04	0.46
boot.p	.000	.000	.000	.000	.000	.083	.010	.000
mean.p	.000	.000	.000	.000	.022	.306	.114	.025
p.upper	.000	.000	.000	.000	.000	.002	.000	.000
p.lower	.003	.001	.000	.000	.185	.961	.677	.211
Power	1.00	1.00	1.00	1.00	0.89	0.23	0.54	0.87
adj mean.p	.001	.000	.000	.000	.032	.353	.144	.036
adj p.upper	.000	.000	.000	.000	.000	.004	.001	.000
adj p.lower	.006	.002	000	.000	.248	.969	.749	.275
adj power	1.00	1.00	1.00	1.00	0.84	0.18	0.47	0.82

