### Data simulation

The data used in the power analyses is based upon semi-bootstrapping. The data is based upon bootstrapped data from the pilot data set. Additional random noise is added to data in order to create a greater deal of variability between each bootstrapped cluster. Crucially, the simulation procedure allows for the specification of intervention main effects on particular dependent variables, making it possible to calculate power of intervention effects under different effect sizes.

The original pilot data set suffers from a lot of missing data, especially in the pretest data set. In particular, there is no language data available in the pretest data. Missing data was therefore interpolated on the basis of regression modelling. This was done by regressing each dependent measure on the background variables and the other dependent measures available. Regression models for each dependent measure were then selected on the basis of backward elimination. These models were then used to predict missing data points. The three language measures (number of unified predicates, number of subordinates and number of events) in the pretest data set were completely interpolated from the posttest data set in this way.

The bootstrapping procedure uses with-replacement random sampling to sample 9 clusters from each intervention group in the pilot data (i.e., 27 clusters in total), each cluster consisting of 12 children. As a result, each bootstrap sample consisted of a total of 324 children. In the bootstrapping of ERP data, cluster sizes ranged from 3 to 7 children, resulting in an average ERP bootstrap sample size of 135.

In order to increase the variation between clusters and individuals, additional random noise within the range of ±0.4 standard deviations, sampled from a uniform distribution, was added to the continuous predictor variables. For ECERS-3 scores, random noise within the range of ±0.5 standard deviations was used. All adjusted variables were trimmed so that any values lying outside the possible range of the variable at hand (e.g., 1–10 for SES) were adjusted to either the minimum or maximum value, and integer variables, such as SES, were rounded to the nearest integer.

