**Fig. 1 Fig1:**
[figure not shown]
The relationship between EFScore and Age in the pilot data set and a bootstrapped data set with noise adjustment set to 0.5 standard deviations. Colours differentiate between children in the original pilot data. Diamonds illustrate data points in the pilot data set and dots show bootstrapped data points. The dashed regression line illustrates the linear fit in the bootstrapped data set, and the dotted line the pilot data set

In addition to adding noise to the data, the dependent measures were adjusted for intervention main effects. This was done by adjusting the difference between the pre-, x_pre_, and post, x_post_ measurements of the aforementioned dependent measures so that they differed in strength in accordance with some adjustable effect size δ. More specifically, the mean difference between pre- and post-measurements was added to each post-measurement data point, i.e., x_post_ = x_post_ + Σx_pre_ / n_pre_ - Σx_post_ / n_post_, in order to ensure no initial difference between mean pre- and post-measurements. Then, the pooled standard deviation over interventions, σ, was calculated. Individual post-measurements were then increased in accordance with its effect size on the basis of the pooled standard deviation, i.e., x_post_ = x_post_ + δσ. Table 3 shows the effect size adjustments used for each intervention and each of the adjusted dependent measures. The table illustrates small, most likely insignificant, effects in the control intervention, strong EF effects but weak language and emotional comprehension effects in the DIL intervention, and, on the other hand, weak EF effects but strong emotional comprehension and language effects in the SEMLA intervention.

**Table 3 Tab3:** Effect size adjustment δ for each intervention and dependent measure

Dependent Variable	Control	DIL	SEMLA
DCCSScore	0.1	0.5	0.3
FlankerScore	0.1	0.5	0.3
HeadShoulders	0.1	0.5	0.3
Math	0.1	0.5	0.3
FDS	0.1	0.5	0.3
TEC	0.1	0.2	0.6
PPVT	0.1	0.3	0.5
LangPredicates	0.1	0.3	0.5
LangSubordinates	0.1	0.3	0.5
LangEvents	0.1	0.3	0.5

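### Table 6 gives power for SES and EF-pretest moderation although the simulation specifies no interaction size; the figures carry pilot slopes forward and are not power for any stated effect

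*Protocol article*

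**What the plan says.** All places are in the protocol article.

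- **What is imposed.** Under Data simulation, "the simulation procedure allows for the specification of intervention main effects on particular dependent variables". After Figure 1: "Individual post-measurements were then increased in accordance with its effect size on the basis of the pooled standard deviation", that is, x_post + δσ. Also, "Table 3 shows the effect size adjustments used for each intervention and each of the adjusted dependent measures". Table 3 has one δ per arm and measure: EF components 0.1 / 0.5 / 0.3 (control / DIL / SEMLA), language components 0.1 / 0.3 / 0.5, TEC 0.1 / 0.2 / 0.6. It has no row for an interaction with SES or with pretest EF.
- **How the data arise.** The procedure is to "sample 9 clusters from each intervention group in the pilot data (i.e., 27 clusters in total), each cluster consisting of 12 children", so that "each bootstrap sample consisted of a total of 324 children". The Power analyses section describes a pilot of very few units, with a single control unit. The number of pilot children is not given.
- **What is concluded.** In the RQ4 section under Power calculations, "moderating effects of SES on EF and Language have very high power under the assumed effect sizes", and "the intervention effects on EF and Language can be expected to be stronger for low-SES children than for high-SES children". Low power for SEMLA × SES on TEC is read there as a sign that no effect will appear.

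**The concern.** Power for an interaction test means something only for a stated interaction size. The article states sizes for main effects and then reports moderation power as if it followed from them. A shift that is the same for every child in an arm raises low-SES and high-SES children equally, so Table 3 says nothing about moderation. What the fitted models pick up must come from somewhere else, and the only other source is the pilot itself.

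SES moderation is one of the main further questions named in the Discussion. A reader who takes 1.00 at face value would treat a null RQ4 result as strong evidence against moderation, and a positive one as confirming a quantified prediction. Neither reading is warranted. Nor does power, high or low, say whether or in which direction an effect exists.

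**Working it through.** **1. Reproduce the printed figures.** Beta.lower and Beta.upper are the 5% and 95% quantiles (Power calculations), so SE = (upper − lower)/(2 × 1.645) and power ≈ Φ(|mean beta|/SE − 1.96).

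| Table 6 column | Mean beta | SE | Ratio of beta to SE | Power from betas | Printed |
|---|---|---|---|---|---|
| EF, DIL × SES | −0.54 | 0.125 | 4.33 | 0.99 | 1.00 |
| EF, SEMLA × SES | −0.53 | 0.106 | 4.98 | 1.00 | 1.00 |
| Language, DIL × SES | −0.79 | 0.106 | 7.43 | 1.00 | 1.00 |
| Language, SEMLA × SES | −0.89 | 0.116 | 7.70 | 1.00 | 1.00 |
| TEC, DIL × SES | +0.65 | 0.234 | 2.78 | 0.79 | 0.89 |
| TEC, SEMLA × SES | +0.24 | 0.207 | 1.16 | 0.21 | 0.23 |
| EF, DIL × EF pretest | −0.23 | 0.112 | 2.04 | 0.53 | 0.54 |
| EF, SEMLA × EF pretest | +0.30 | 0.100 | 2.99 | 0.85 | 0.87 |

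The four values of 1.00 agree with the table's own betas. Two other columns fit the normal approximation less well (0.79 against 0.89, 0.85 against 0.87). The issue is where the betas come from.

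**2. Do the betas depend on Table 3?** Adding δσ to every post score in an arm changes that arm's intercept. The slope of the post score on SES, or on pretest EF, within the arm stays the same, and so do the slope differences between arms. As a numerical check for SES, one artificial pilot was resampled with the same random seed under δ = (0, 0, 0), (0.1, 0.5, 0.3) and (0.1, 2, 3). All three gave identical interaction betas (−0.187 and −0.131) and identical rejection rates (0.51 and 0.28). The assumed effect sizes have no bearing on the SES moderation power.

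**3. Where do they come from?** Children are drawn with replacement within each pilot arm: 9 × 12 = 108 per arm, 3 × 108 = 324 in all. Each arm's pilot slope is carried into every sample and tested as if it rested on 108 independent children. The added noise ("additional random noise within the range of ±0.4 standard deviations, sampled from a uniform distribution, was added to the continuous predictor variables") puts in no moderation.

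**4. What does the procedure return when there is no moderation?** Simulated pilots with zero true interaction were resampled to 108 per arm, with noise on SES and the Table 3 shifts for EF, and arm × SES plus pretest was fitted. Assumptions: ordinary least squares in place of the mixed model, pre-post correlation 0.6, pilot size varied. Ranges cover runs with and without added outcome noise.

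| Pilot children per arm (assumed) | Mean 'power' | Share of interactions at 0.80 or more | Share at 0.95 or more |
|---|---|---|---|
| 8 | 0.61–0.62 | about 49% | about 39% |
| 12 | 0.51 | about 33% | about 22% |
| 15 | 0.48–0.53 | 30–34% | 21–24% |
| 20 | 0.41–0.46 | 22–26% | 10–15% |
| 30 | 0.33–0.36 | about 14% | 6–8% |

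Fresh samples of 108 per arm with only the Table 3 shifts rejected in 0.051 and 0.049 of runs, the nominal 5%.

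**5. Signs in Table 6 itself.** High 'power' also goes to interactions against the hypotheses: DIL × SES on TEC is +0.65 (0.89), and SEMLA × EF pretest is +0.30 (0.87), although negative EF moderation is hypothesised for both arms. The text notes the first but not the second. The near-equal DIL and SEMLA betas (−0.54 and −0.53; −0.79 and −0.89) are what one shared control slope would produce.

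**6. The closing sentence.** The text gives the positive TEC coefficient to DIL, as Table 6 does, and then draws its conclusion about SEMLA.

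**The case against.** A reader might infer that the Table 6 interactions are mere pilot noise. The document does not support that. The resampled data do contain moderation, namely the pilot's own; what is missing is a specified size. Scaling the ratios in step 1 back by √(n/108) gives the following, with pilot size n per arm assumed:

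- EF: z of about 1.4 to 1.7 at n = 12 and 1.9 to 2.1 at n = 20.
- Language: about 2.5 to 2.6 at n = 12 and 3.2 to 3.3 at n = 20.

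The EF values are compatible with chance. The Language values are hard to put down to chance at those sizes, although the three narrative pretest measures were wholly interpolated from posttest data, which could itself distort the slopes. Without the pilot data the question stays open.

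A reader might also infer that 0.05 is the correct power. It is the type I error rate when moderation is zero. No correct power can be given, because no interaction size is stated.

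It is also fair to say that the low-SES hypothesis was set from earlier studies and not from Table 6, that the article reports the low power for SEMLA × SES on TEC and flags one sign as contrary to its hypothesis, that it calls the design partly exploratory, and that no stated sample-size decision or test depends on Table 6. This limits the consequences. It does not supply the missing interaction size, and it does not justify reading power as a prediction.

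**Conclusion.** The point holds in this form: Table 6 does not report power under the assumed effect sizes, because those sizes do not enter the moderation coefficients. It reports the SES and EF-pretest slopes of a few pilot units at an enlarged sample size. That rests on the document's own description and on simple algebra. The predictions drawn from it, that low-SES children will gain more on EF and Language and that SEMLA × SES will show nothing on TEC, do not follow.

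The size of the distortion is an illustration: mean 'power' of about 0.33 to 0.62 against 0.05 with no true moderation, under an assumed 8 to 30 pilot children per arm, least squares and a pre-post correlation of 0.6. The real power of the RQ4 tests is unknown and could be high or low. The fault affects the reported figures and their interpretation; it does not invalidate the RQ4 models themselves.

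**What to change.** Either withdraw the Table 6 power figures and the two predictive statements, and say that the power of the RQ4 tests is unknown; or rerun the simulation with stated interaction sizes for SES and pretest EF. A rerun should include a zero-interaction run that must return about 5%, and should report the smallest interaction the trial can detect with adequate power. In either case, correct the closing sentence of that section so that the positive SES coefficient on TEC is attributed to DIL, and mention that SEMLA × EF pretest runs against its hypothesis.

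Cost: text edits and, for the second route, one simulation rerun. No data collection or analysis model changes. The stated power is likely to become less favourable.
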